### Testing procedure

Methodological planning stipulates all anthropometrical, foot and motor performance measurements to be performed during a physical education lesson. Prior to the testing, a physical activity questionnaire for children/adolescent (PAQ-C and PAQ-A [25, 26]) and a barefoot questionnaire will be distributed by the teachers and collected by the study staff on the testing day and briefly checked for completeness. All children bringing the signed consent form and voluntarily want to participate will be gathered and all relevant information for the testing will be given by the principal investigator. After a short warm up period (jogging for < 5 min), participants will be randomly allocated to the seven testing stations:AnthropemetryFoot caliperPressure plate20 m sprintingLateral jumpingStanding long jumpBackwards balancing

After their first testing station, a participant will be transferred to the next vacant station without a fixed order. Testing station 1–3 will be completed only barefoot, while testing stations 4–7 will be performed in barefoot and shod conditions. The order of the condition is randomized a priori on the registration sheet which is distributed to the participants on the testing day. A flowchart displaying the participant flow through the study is shown in Fig. 1.

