**Fig. 3 Fig3:**
[figure not shown]
Heel to toe length, foot width and dorsum height measurements will be obtained using a specially constructed platform. Dorsum height will be measured at 50 % of the heel to toe length using the sliding caliper pictured on the right foot in this picture. Static arch height index will be defined as the ratio of dorsum height and heel to toe length

$$ Static\  arch\  height\  index = \frac{Dorsum\  height}{Heel-to- toe\  length} $$

Feet of the participants will be measured at sitting (10 % of body weight (BW)) and standing (50 % of BW) and the pliability ratio will be calculated according to Kadambande et al. [20]:$$ Pliability\  ratio = \frac{HTL\ 50\%\  of\ BW \times FW\ 50\%\  of\ BW}{HTL\ 10\%\  of\ BW \times FW\ 10\%\  of\ BW} $$

Foot strike patterns will be captured during 20 m jogging and both sprinting trials in each condition at the 17.5 m mark using a wide-angle high speed camera (GoPro HD Hero 4, GoPro Inc., San Mateo, California, USA). The camera will be positioned 150 cm from the midline orthogonal to the marked running way and set to record 120 frames per second at a resolution of 1280 × 720 pixels. After testing, videos will be processed using a video editing software (Adobe Premiere Pro CS 6, Adobe Systems, San Jose, California, USA) and rated independently by two reviewers, with a third experienced reviewer for consensus. A rearfoot strike is defined as a first ground contact with the heel or the rear third of the foot, while a forefoot strike is present when the anterior part of the foot first contacts the ground. For a midfoot strike heel and anterior part of the foot contact the ground simultaneously. This method has been used successfully in other studies to determine the foot strike pattern [33].

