#### Motor performance

Participants will complete multiple tests to assess motor performance; 20 m sprint [34], lateral jumping, standing long jump, and backwards balancing [35]. Each station will be performed in two conditions: barefoot and wearing sport shoes.

Preceding the lateral jumping (Additional file 3), participants will stand in one half of a square next to a line, indicated on the floor by masking tape. He/she will be instructed to jump sideways as fast as possible for 15 s. One minute rest will be given between the two trials per condition and the average score of each condition will be used for analysis. For the standing long jump (Additional file 4), a participant will be instructed to stand with their toes adjacent to a labelled start line, bend at the knees whilst swinging the arms backwards and subsequently, jump as far as possible on to a soft rebounding mat. One of the researchers will place a rod at the most posterior of where the participant landed and will read off the distance on the measuring tape attached parallel to the rebound mat on the floor. This will be repeated three times per condition and the distance of the best trial per condition is used for analysis. A sprinting lane of 20 m (Additional file 5) will be indicated on the floor by a start line labelled by tape and two pylons at 0, 10 and 20 m, as well as one meter after the 20 m mark as a dummy. A time sensor device will be placed at the start, 10 and 20 m. In Germany mobile magnetic timing gates from Humotion SmarTracks (Münster, Germany) will be used and Brower Timing Systems speed gates (Salt Lake City, UT, USA) in South Africa. The 10 m and 20 m time of the best trial per condition will be used for analysis. Lastly participants will be asked to walk backwards (Additional file 6) over a 6 cm, 4.5 cm and 3 cm wide balance beams with, respectively, 2 trials per beam [35]. The first step after the starting position will not be counted, every subsequent step will then be counted until one foot touches the ground or a maximum of 8 steps per beam is achieved. The children will be instructed to look up straight (with an X on eye level) and put their next step directly behind the other foot. The scores of two trials on each of the three beams will be added to a total score per condition for analysis (max 48 points).

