### Statistical analysis

Descriptive data will be presented using descriptive statistics. The participant’s barefoot questionnaire and the PAQ outcomes will be compared to all attending children in 2 primary (1 rural, 1 urban) and 2 secondary schools to assess external validity. The outcome measures will be evaluated for normality using Shapiro-Wilkins and visually using P-P plots, if possible, non-normal distributed data will be adjusted. Mixed Models linear regression will be used to assess if the foot mechanical and motor performance outcomes differ between the barefoot and the shod participants (fixed factors). Furthermore, we will test differences due to being barefoot or shod change by age by adding an interaction of age*group to the linear regression. Differences in foot strike pattern during jogging and sprinting between barefoot and shod participants will be assessed using ordinal regression. The school of a participant will be added to the model as a random effect in order to adjust for possible differences between the schools and their geographical location. Furthermore, Gender, BMI, PAQ-Score, ethnicity and inside/outside testing will be tested for confounding in all models (regression coefficient changes >10 %). We hypothesize that older boys could have higher arches (lower dAI) [37] and perform better on motor performance tasks, while girls’ feet will show a higher pliability. BMI increases the dAI and possibly decreases motor performance [38, 39]. A higher level of physical activity (higher PAQ score) is probably related to better motor performance. And lastly, Caucasians could have higher arches (lower dAI) [40].

We anticipate that gender might modify the effect of being barefoot or shod on the outcome measures and therefore gender will additionally tested as an effect modifier (interaction between outcome and gender *p* < 0.1). In all cases, a significance level of 5 % is pre-stipulated.

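### Body height is missing from the listed confounders for standing long jump and sprint, so a height difference between barefoot and shod children left at equal age, sex, ethnicity and BMI would bias the group coefficient, in either direction.

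*Protocol article*

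**What the plan says.** All references are to the protocol article.

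- **Outcomes.** Under Motor performance, for the standing long jump "the distance of the best trial per condition is used for analysis". For the sprint, "The 10 m and 20 m time of the best trial per condition will be used for analysis". Neither is divided by height, leg length or any other measure of size.
- **Model.** Under Statistical analysis, a linear mixed model compares barefoot with shod participants. Age dependence is tested by "adding an interaction of age*group to the linear regression". In addition, "The school of a participant will be added to the model as a random effect".
- **Confounders.** "Gender, BMI, PAQ-Score, ethnicity and inside/outside testing will be tested for confounding in all models", the criterion being "regression coefficient changes >10" %. The list is specific and meant for every model. Height appears nowhere as a covariate, a scaling variable or a limitation.
- **Availability of height.** The Testing procedure section plans for "all anthropometrical, foot and motor performance measurements to be performed during a physical education lesson", and anthropometry is one of the seven stations. The article does not say in words that height is measured, but BMI cannot be computed without it.
- **Foot outcomes.** These are ratios by definition. For example, "Static arch height index will be defined as the ratio of dorsum height and heel to toe length".

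**The concern.** Jump distance and sprint time can be expected to depend on stature, also among children of the same age. Footwear habit is tied largely to country: the Study design section explains why recruitment is split by region, and the Discussion describes German children as shod most of the time. Children from two countries may differ in height for age. If they do, part of the group coefficient for leg power and speed would reflect stature rather than barefoot habit. Height is not a plausible consequence of going barefoot, so adjusting for it would remove none of the effect under study.

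The listed terms do not cover this:

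- **Age** removes average growth, not a height difference at equal age.
- **BMI** is weight divided by height squared and says little about stature.
- **School** as a random effect cannot absorb a difference between countries, because each school lies in one country.
- **The 10% rule** can select only from variables on the list.

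At stake are the between-group results for standing long jump and for the 10 m and 20 m sprint.

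**Working it through.** **1. The plan's own figures.** The Sample size section gives a standing long jump mean of 152.9 and SD of 31.5, with n = 18. It sets the minimal important difference at 20% of the mean for the dynamic arch index. I assume the same rule for the jump: 0.20 × 152.9 = 30.58 cm. At two-sided alpha 0.05 and power 0.80,

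n = 2 × (1.960 + 0.842)² × (31.5 / 30.58)² = 16.7, that is 17 per group, or 18 with the t distribution.

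This matches the stated 18. For the 20 m sprint (mean 3.81, SD 0.64), 20% is 0.762 s and the formula gives 11.1, that is 12, as stated (13 with the t distribution). The 20% yardstick is therefore a fair reading for both outcomes.

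**2. Size of the bias.** Bias = residual height difference × slope of the outcome on height. The documents give neither input, so both are assumptions.

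- Jump: 2-4 cm × 0.5-1.5 cm per cm = 1-6 cm. Against 30.58 cm this is 3% to 20%. The mid case, 3 cm × 1 cm per cm, is 3 cm, or 10%.
- 20 m sprint: 2-4 cm × 0.005-0.015 s per cm = 0.01-0.06 s. Against 0.762 s this is 1% to 8%.

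**3. Chance of a significant result with no true barefoot effect.** The protocol plans 20 children per age group per country; 13 ages × 20 = 260 per country. I assume 260 per footwear group. Without clustering, SE = SD × √(2/260): 31.5 × 0.0877 = 2.76 cm for jump and 0.64 × 0.0877 = 0.056 s for sprint.

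For clustering I assume ten schools per country, so about 26 children per school, and an intraclass correlation of 0.05. The design effect is 1 + 25 × 0.05 = 2.25, and the SE is multiplied by 1.5, to 4.14 cm and 0.084 s.

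The rejection probability is Φ(bias/SE − 1.96) + Φ(−bias/SE − 1.96).

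| Outcome | Bias | No clustering | Design effect 2.25 |
|---|---|---|---|
| Jump | 1 cm | 6.5% | 5.7% |
| Jump | 3 cm | 19% | 11% |
| Jump | 6 cm | 58% | 30% |
| 20 m sprint | 0.01 s | 5.4% | 5.2% |
| 20 m sprint | 0.06 s | 19% | 11% |

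A residual SD below 31.5 cm, once age is in the model, would raise the jump rates. With an assumed SD of 20 cm and no clustering, a 3 cm bias gives 40%. The size of the bias does not depend on the SD.

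**4. Do age, sex and BMI already deal with it?** A simulation used 520 children, no true barefoot effect, a slope of 1 cm of jump per cm of height, a height-BMI correlation of 0.3 and a residual SD of 18 cm, without clustering; all of these are assumptions. With age, sex and BMI in the model, the mean spurious group effect was 1.9 cm for a 2 cm height difference and 3.9 cm for 4 cm. Nearly all the bias remained. Adding height brought it to about zero.

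**The case against.** The strongest reply is that the analysis is already adjusted and the harm is hypothetical.

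- **Adjustment.** A reader might infer that jump and sprint are compared raw between two nations. They are not. Groups are defined by a footwear questionnaire, age is in the model, and gender, BMI, activity, ethnicity and testing site are candidates. The Discussion also plans to recruit South African children of ethnic background similar to the German children. Gender and ethnicity may absorb part of a height gap. This stands, and it limits the point to what remains after them.
- **No evidence of a height difference.** A reader might infer that stature will be reported as a barefoot benefit. The documents give neither a difference nor its direction. If shod children were taller, the bias would work against the authors' hypothesis and could hide an effect. This stands.
- **The rates.** The upper figure of 58% could be taken for the study's error rate. It rests on assumed inputs and ignores clustering, whereas the planned model has a school effect. The 260 per group is also an assumption: the plan fixes numbers per country, not numbers meeting the barefoot definition. This stands.
- **Consistency.** The foot measures are ratios by definition, while distance and time are the scores of established tests. The contrast shows no contradiction. This stands too; leaving the scores unscaled is acceptable if height is in the model.
- **Limits of the remedy.** Height tracks age closely between 6 and 18 years, and other country-level differences would remain. Both are true, but neither shows that adding height does harm to the group comparison.

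**Conclusion.** The point holds as a gap in the covariate list, not as a demonstrated bias. The plan names its candidate confounders for all models and omits height, while two kinds of motor outcome that can be expected to depend on height are analysed unscaled. Neither age, BMI nor the school effect would remove a stature difference at equal age.

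If such a difference remains after sex, ethnicity and BMI, the group coefficient is biased, with unknown sign. Under the assumed inputs the jump bias is 1-6 cm, well below the 30.6 cm that corresponds to 20% of the mean. It is therefore unlikely by itself to produce a difference of that size, but it could produce or mask statistical significance in the pooled sample: about 7-58% false positives without clustering and about 6-30% with a design effect of 2.25. The sprint bias is smaller relative to its yardstick.

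The comparison of barefoot and shod conditions within the same child is unaffected, since height is the same in both.

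**What to change.** In the Statistical analysis section, add body height as a prespecified covariate, alongside age, in the between-group models for standing long jump and for 10 m and 20 m sprint time. Enter it regardless of the 10% rule, so that its inclusion does not depend on the observed change in the coefficient. Report the group estimate without height as a sensitivity analysis, so that readers can see how far stature matters.

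The cost is a sentence or two of analysis wording. Height has to be obtained for BMI anyway, so there is no added field work, and no stated sample size changes. The downside is that height is correlated with age: the age terms, including the interaction with group, become somewhat less precise and must be read as conditional on height. Other differences between the two countries are not addressed by this change and remain a limitation to state.

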**Methods:**

This study has a cross-sectional, binational design and is part of the “Barefoot Locomotion for Individual Foot- and health Enhancement (Barefoot LIFE)” project. Two large cohorts (n_(total)_ = 520) of healthy children and adolescents between 6 and 18 years of age will be included respectively in Germany and South Africa. A barefoot questionnaire will be used to determine habitually barefoot individuals. The testing will be school-based and include foot mechanical (static arch height index, dynamic arch index, foot pliability) and motor performance (coordination, speed, leg power) outcomes. Gender, BMI and level of physical activity will be considered for confounding.

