### Sample size

Although we did not opt to distinguish primary or secondary outcome measures, the dAI was used to enable a sample size calculation. Muller et al. [36] has shown that the average dynamic arch index (μ: 0,19) and the accompanying standard deviation (SD: 0065) are stable between the ages of 6 and 13. The minimal important difference was set at 20 % of the average (0.19; i.e., 0.038). With a two-sided significance level of 0.05, and assuming a power of 0.8, a minimum of 16 participants per age group, per country, had to be included for this study. Due to the diversity of the study, additional power calculations have been performed. Based on the arch height ratio derived from Waseda et al. [22] the sample size for arch height ratio (navicular height*100/foot length) should be *n* = 12 per age group (μ = 15,0; SD = 2,6). Furthermore, based on a preliminary study on children, the sample size based on the standing long jump should be *n* = 18 (μ = 152,9; SD = 31,5), for lateral jumping *n* = 22 (μ = 38; SD = 9,2) and for 20 m sprint *n* = 12 (μ = 3,81; SD = 0,64). Therefore, our *n* = 20 per group seems to be sufficient. In order to allow for these differences and other unknown variances within the other variables we choose to increase the number from 16 to 20 participants per age group, per country.

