Similar differences in the level of barefootness are found in other studies. For instance, UB Rao and B Joseph [15] compared barefoot children to shod children in India where the latter group mainly wore flip-flops or shoes with a soft upper. One could argue that the influence of these ‘shoes’ is not comparable to wearing hard soled shoes with a rigid upper. Other studies compared participants who were shod or barefoot all of the time, but those participants were from different ethnicities [14, 16, 20]. Our study will aim to recruit participants in South Africa from similar ethnic backgrounds to the German children. This will allow for increased comparability of the independent variable: being habitually barefoot or shod. However, the diverse ethnic backgrounds of the South African population will not allow for an exact similar recruitment compared to the German population. We will adjust for this discrepancy by adding ethnicity as a confounding variable to the statistical evaluations. And lastly, even though we think that the use of a barefoot questionnaire is preferable compared to the mentioned studies in assessing the level of barefootness, a limitation of the use of the questionnaire is that it will not be validated a priori.

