### Foot mechanics

A major purpose of this study is the assessment of the foot mechanics. Differences in foot anthropometrics have been found between habitually barefoot and shod individuals [8, 14, 16]. Special focus will be laid on the medial longitudinal arch and its development over age. Most studies report that the development of the arch mainly occurs until the age of 6–8 years [42], while other studies state that substantial changes to the arch morphology can still occur during adolescence [43]. Intrinsic and extrinsic (e.g., footwear) factors influence the development of the foot [42] and thus the habitual footwear use will be examined.

The classification and measurement of foot mechanics is still a controversial topic [44, 45]. Indirect (footprints analogue or digital pedobarographic) and direct methods (clinical assessment, caliper, radiographs) exist with certain strengths and limitations within each method. In this study we will assess the foot mechanics using a dynamic indirect (pedobarographic) and a static direct method (caliper). The pedobarographic measurement of the arch index has been shown to be a simple and reproducible method [46] that show higher reliability than navicular height measurement in pediatric populations [47]. Nonetheless, there is variability in the dynamic arch index and we will address this problem by including three valid trials per leg in each participant using a two-step protocol that has been shown to be reliable for children [29, 48, 49]. Invalid trials will be defined by the trained investigator when participants target the platform, step on the border or alter their gait for example due to distraction by the other children. In that case the trial will be excluded and re-measured. Using digital pedobarographic measures and the derived dAI is a proxy for the longitudinal medial arch. It has been hypothesized that dAI might be influenced by other variables than the skeletal arch itself, for instance the amount of adipose tissue [38]. A radiographic measure (X-ray) of the arch would be a more valid measure. But besides the exposure to radiation, this method is not feasible while testing in the field with the current sample size of the study. Thus, the non-invasive static and dynamic arch assessment used in this study will be preferred. By statistically adjusting for BMI, we aim to increase validity of the dAI measure.

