### Motor performance

The criterion for the selection of these motor performance tests is related to the expected effects of habitual barefoot locomotion on lower limb gross motor skills, even though the evidence for the effects of habitual barefoot locomotion on motor performance is unclear [[name], Heidt C, [name], [name], [name]. Long-term effects of habitual barefoot running and walking: a systematic review. Manuscript submitted for publication].

The tests used to assess motor performance have been used in other studies, and have been shown to be valid and reliable [34, 35]. Even though all tests have been extensively practiced by the main researchers, the researchers from both countries combined and separate, it is imaginable that regional characteristics and the use of different examiners as well as test equipment will influence the results. An example is that the sprinting will be mostly done outdoors in South Africa due to a lack of indoor sport facilities at some schools which might be influential on the 10 m and 20 m sprint time. By adding a variable for outdoor/indoor running we will test if it acts as a confounder and adjust the outcome accordingly. Another difference between testing in Germany and South Africa is the speed gates used. Mobile magnetic timing gates will be used in Germany while in South Africa single beam speed gates will be used [53]. The latter is less accurate, however, the measurement error is still small (0.01 s) [54]. Therefore, no adjustments will be made when comparing the two countries.

Another limitation could be that measuring the distance during the standing long jump is done visually by one of the researchers by placing a right-angled rod at the place the heel landed. By using the average of three tries the influence of possible random measurement errors would decrease. Nonetheless, to provide comparability to other studies [34, 35], we will use the best of three tries. When using the backward balance test, a possible limitation would be a ceiling effect since there is a maximum of 8 steps per beam. However, by adding the steps for all the beams and the likelihood of not reaching the maximum 8 steps on the 4.5 and 3 cm beam, it is unlikely that a ceiling effect will occur. The score (i.e., the sum of the trials) will be treated as a continues variable during data analysis.

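### The 10% change-in-coefficient rule conflicts with the unconditional adjustment promised for ethnicity and for BMI in the dAI analysis, and age is not named in the main barefoot-shod comparison

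*Protocol article*

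**What the plan says.** The main analysis is a mixed linear regression comparing barefoot with shod participants, with school as a random effect (Methods/Design, Statistical analysis). On covariates that section says: "Gender, BMI, PAQ-Score, ethnicity and inside/outside testing will be tested for confounding in all models (regression coefficient changes >10" per cent).

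Elsewhere the protocol article says:

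- **Ethnicity** (Discussion, Barefoot questionnaire), on the ethnic mismatch between the two countries: "We will adjust for this discrepancy by adding ethnicity as a confounding variable to the statistical evaluations".
- **BMI** (Discussion, Foot mechanics): "By statistically adjusting for BMI, we aim to increase validity of the dAI measure".
- **Abstract, Methods:** "Gender, BMI and level of physical activity will be considered for confounding". Ethnicity is not listed there.
- **Indoor or outdoor testing** (Discussion, Motor performance): "we will test if it acts as a confounder and adjust the outcome accordingly".
- **Age** (Statistical analysis): it enters by "adding an interaction of age*group to the linear regression". It is not in the list of candidate confounders and is not named in the group comparison that precedes the interaction.
- **Age in the design** (Sample size): "we choose to increase the number from 16 to 20 participants per age group, per country".

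**The concern.** Two instructions for the same covariates disagree. An analyst who finds that ethnicity shifts the group coefficient by 8% must leave it out under Statistical analysis and keep it under the Discussion.

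These are not minor covariates. The Background criticises earlier studies for mixing ethnic backgrounds. The Discussion concedes that recruitment cannot match ethnicity across the two countries. Statistical analysis itself expects that "Caucasians could have higher arches (lower dAI") and that BMI raises the dAI. Confounders named in advance should not have to pass a test on the study's own data.

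The form of the rule adds a second problem. The threshold is a fraction of the estimate, so the same covariate can be kept when the group effect is small and dropped when it is large. With many outcomes and none designated primary, each could end up with a different adjustment set.

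Age is the third problem. The article expects older boys to have higher arches and to perform better on the motor tasks. If age is absent from the model that gives the overall group difference, any age difference between the groups passes into that estimate.

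**Working it through.** **1. The sections side by side**

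| Covariate | Statistical analysis | Elsewhere | Compatible? |
|---|---|---|---|
| Ethnicity | only if change >10% | unconditional (Discussion, Barefoot questionnaire) | No |
| BMI, dAI outcome | only if change >10% | unconditional (Discussion, Foot mechanics); conditional (Abstract) | No |
| Indoor/outdoor | only if change >10% | conditional (Discussion, Motor performance) | Yes |
| Age | interaction only | equal numbers per age and country (Sample size) | Main-effect term not stated |

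**2. Age balance**

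The planned total reproduces: 13 ages × 2 countries × 20 = 520. That balances age between countries. Group, however, is set by questionnaire. Primary pupils qualify on current habits at home and at school or in sports. Secondary pupils qualify on recalled primary-school habits plus current habits at home. Balance by country therefore does not guarantee balance by group. The documents give no barefoot share by age, so no imbalance can be calculated.

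**3. The most that one omitted candidate can leave**

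Inputs are from Sample size: a minimal important difference of 0.038 for the dAI, and an SD printed as 0065, read here as 0.065 (assumption). I also assume 260 v 260 independent children.

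- Standardised effect: 0.038/0.065 = 0.585 SD.
- SE = 0.065 × √(2/260) = 0.0057.
- 10% of the effect = 0.0038, and 0.0038/0.0057 = 0.67 SE.
- Non-coverage of a 95% interval at that shift: P(|Z + 0.67| > 1.96) ≈ 0.10.

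This is a ceiling for one screened covariate sitting at the threshold. School clustering would enlarge the SE and reduce the ratio. Five covariates screened singly, each just under 10% and all in the same direction, could leave 1 − 0.9⁵ = 41% to 1.1⁵ − 1 = 61%. That is an extreme case.

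**4. How the rule behaves**

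Simulation with one standardised covariate, 260 v 260 and no school effect; the covariate effects and imbalances are assumed.

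| True group effect | Covariate effect | Imbalance | Covariate kept | Bias left |
|---|---|---|---|---|
| 0.585 SD | 0.3 SD | 0.1 SD | 12% of runs | 0.022 SD (0.022/0.585 ≈ 4%) |
| 0.585 SD | 0.3 SD | 0.3 SD | 77% | 0.013 SD (0.013/0.585 ≈ 2%) |
| 0 | 0.3 SD | 0.1 SD | 90% | near 0 |
| 0 | 0.3 SD | 0.3 SD | 100% | near 0 |

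The first and third rows have the same confounding. Whether the covariate is kept changes from 12% to 90% only because the group effect differs.

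**5. Precision**

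Fixed adjustment for a balanced covariate multiplies the SE by √(1 − R²): 0.95 at R² = 0.1, 0.84 at 0.3 and 0.71 at 0.5. In the simulation with a balanced covariate of R² = 0.36 (effect 0.6 SD, 0.6² = 0.36):

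- at 0.585 SD, the empirical SD of the estimate was 0.076 under the rule and 0.072 with fixed adjustment (0.0763/0.0715 = 1.07);
- at 0.2 SD, power was 77% under the rule and 81% with fixed adjustment.

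**6. Cost of fixing ethnicity in the model**

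If group and ethnicity have correlation r, the SE is multiplied by 1/√(1 − r²): 1.15 at r = 0.5 and 1.40 at r = 0.7.

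**The case against.** **The Discussion sentences may be shorthand.** The Abstract and the indoor/outdoor sentence describe the same conditional procedure as Statistical analysis, so the ethnicity and BMI sentences could be loose wording for it. The BMI promise also covers the dAI only. This narrows the conflict but does not remove it: the ethnicity sentence offers adjustment as the remedy for an admitted recruitment mismatch, which a conditional test does not guarantee.

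**A stated change-in-estimate threshold is a recognised way to select confounders.** That is true, and it tends to retain strong confounders. Near a zero effect it keeps almost everything, so there it resembles full adjustment. What remains is the dependence on effect size and the loss of balanced predictors.

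**Age is in the analysis.** A reader might infer that age is ignored. The documents do not support that: the age-by-group interaction is planned, age dependence is a stated aim, and a condensed article need not spell out the main effect that goes with an interaction. School as a random effect may also absorb part of the age variation. For the dAI, Sample size calls the mean and SD stable from 6 to 13. What stands is that the main barefoot-shod comparison does not name age.

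**Fixed adjustment is not free.** Ethnicity may widen the interval, so the case for it is validity and not precision. PAQ score may lie on the path from barefoot habit to motor performance, so forcing it into every model is debatable.

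**Conclusion.** The conflict over ethnicity, and over BMI for the dAI, is in the current text and needs no assumption. The missing age term in the main comparison is also a matter of text; whether it biases anything depends on the age mix of the two groups, which the documents do not give.

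The numerical consequences of the 10% rule are modest and rest on assumed values: at most about 10% of the effect from one omitted candidate, 2-4% in simulation, and about a 7% larger standard deviation for a strong balanced predictor.

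Three stronger readings are not supported:

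- **The tests do not hold their 5% level.** In the single-covariate runs at zero effect, rejection was 3.6-4.9% under the rule and 3.6-5.2% with fixed adjustment.
- **A bias of 0.67 SE is to be expected.** It is a ceiling and ignores school clustering.
- **Leaving age out wastes a large share of the sample.** That needs an R² for age, which the documents do not give.

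The plan should be changed, because the change is simple and protects against confounders that the authors themselves name. The point does not invalidate the design.

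**What to change.** 1. Enter age, gender, BMI and ethnicity in every main model as prespecified fixed covariates, whatever their effect on the group coefficient. State the age main effect explicitly, both in the group comparison and alongside the age-by-group interaction.
2. Add indoor/outdoor testing for the tests it affects.
3. Report models with and without PAQ score as a sensitivity analysis, because it may be a mediator.
4. Keep the 10% comparison only as a description of crude against adjusted estimates.
5. Reconcile Statistical analysis with the two Discussion passages on ethnicity and BMI.

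The covariates are already planned for collection, so the work is a change of wording. The cost is a few degrees of freedom out of 520 children, and a wider interval for the group effect if ethnicity is strongly correlated with group. That widening should be reported and not avoided by dropping ethnicity.
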